### Interventions

#### Strength training

Both strength training interventions consist of a 5-min warm-up, 40-min training, and 15-min cool-down. The 60-min sessions are conducted 3 times^.^wk^-1^ for 18 months at the Wake Forest Clinical Research Center. Each group session will include between 12–24 participants (1 to 2 waves) and will be supervised by two American College of Sports Medicine certified exercise interventionists and a number of undergraduate interns. The first two sessions introduce participants to proper techniques, and at the third, 1-repetition max (1RM) tests determine the starting resistance used for each exercise in the subsequent sessions until the next assessment (detailed below). Intensity (load) is defined as %1RM [8]. The reliability of our 1RM testing for 12 older adults with knee OA tested twice one week apart was: leg press, ICC = 0.95; leg curl, ICC = 0.99; and leg extension, ICC = 0.98. Each exercise is performed on a Nautilus resistance-training machine with 60–90 s of rest between sets; 1RM is defined as the maximum weight one can lift in a single repetition. Participants will keep a session log of each resistance exercise, its weight setting, and number of sets and repetitions achieved. Although our hypotheses focus on the lower extremity, experience indicates that participants want a well-rounded program. Thus, for both groups the program includes 6 lower body exercises with each leg exercised separately to prevent an unequal distribution of load between the least affected and most affected sides: hip abduction and adduction; leg curl, extension, and press; and seated calf; and 4 upper body and core exercises: compound row, vertical chest, lower back, and abdomen. We use Nautilus machines based on time, safety, and availability, but results will be generalizable to most strength training methods. Participants perform a 5 minute warm-up on either the walking track or a stationary bicycle and, at the completion of each strength training session, a 15 minute cool-down consisting of various upper and lower body stretching exercises.

Participants who plan absences of >2 sessions use Thera-Bands in a home-based program. Upon their return, interventionists determine the progression needed to reach prior intensity.

Previous strength training trials with older adults predict small fluctuations in body weight (< 1 kg) as muscle mass increases and fat mass decreases [44]. Interventionists are alert to any substantial change (≥ 2 kg) and, if necessary, the participant is referred to the medical director.

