### Trial conduct

#### Recruitment

The 30-month recruitment period is divided into 10 waves of approximately 37 participants each, entering the study at 3-month intervals. The predominant recruitment strategy is newspaper advertisements. Other recruitment efforts include mass mailings, presentations at local aging service networks, senior centers, churches, radio, and on-line advertising. Our Claude D. Pepper Older Americans Independence Center recruitment core also has access to a large database of older adults who have consented to be contacted about participation in clinical trials. Specific strategies aim to maximize the number of African Americans who qualify for, and are enrolled in, the study. At biweekly meetings, all recruitment activities and the number of participants randomized are reviewed.

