#### Sample-size calculations

##### Primary outcomes

A total sample of 372 (124/group) provide 80% statistical power to detect differences ≥17.6% in pain and ≥9.6% in maximal compressive force at the 2-sided 0.0083 significance level with 80% retention (2-sample *t*-test, Nquery Advisor). Standard deviations for pain and maximal compressive force were obtained from the START pilot (unpublished) and ADAPT [58,59] which measured the same outcomes and used similar patient populations; with mean differences of 1.12 (18%) and 657 N (20%), respectively.

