##### Secondary outcomes

Overall, our sample size provides a moderate effect size of 0.46 with relevant detectable differences. ADAPT’s largest effect on WOMAC function was a 17% relative decrease. We are able to detect differences in thigh-muscle volume smaller than 10%. Goopaster [92] showed that after 12 months mean thigh-muscle attenuation significantly decreased by 1.4 HU in a control group but not in a physical activity group. With 6 more months of physical activity, we expect to detect group differences as small as 2.3 HU. A magnitude of 22% reduction in IL-6 is similar to reductions seen in clinical trials of statins and other anti-inflammatory medications [93-98].

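### Strength training is delivered in groups of 12–24, but the stated model and power calculation make no allowance for correlation within a training group

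*Protocol article*

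**What the plan says.** **Delivery.** The Strength training section describes 60-minute supervised sessions, three times a week for 18 months: "Each group session will include between 12–24 participants (1 to 2 waves"). The Recruitment section states: "The 30-month recruitment period is divided into 10 waves of approximately 37 participants each". The Timeline section gives the average as 37.2 per wave. Controls attend organised workshops with small-group discussion (Healthy living education), but no workshop size or wave assignment is given. Techniques to improve adherence and retention names group dynamics among the sources of the design.

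**Analysis.** Under Primary aim, the mixed model contains time (6 and 18 months), treatment, their interaction, gender, baseline BMI and the baseline outcome, fitted by maximum likelihood with an AR(1) covariance. Secondary aims uses the same adjustments. Wave, training group and interventionist do not appear.

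**Power.** Sample-size calculations, Primary outcomes: "A total sample of 372 (124/group) provide 80% statistical power to detect differences ≥17.6% in pain", and this "at the 2-sided 0.0083 significance level with 80% retention". The method is given as "2-sample *t*-test, Nquery Advisor". The Secondary outcomes paragraph adds: "Overall, our sample size provides a moderate effect size of 0.46 with relevant detectable differences".

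**The concern.** Participants are randomised individually, but those in the strength arms then train together for 18 months with the same companions and supervision and over the same calendar period. If sessions are arm-specific, training group is nested within arm. An effect shared by a group then does not cancel in a treatment contrast; it adds to the contrast's variance. An AR(1) structure over two visits describes correlation within a person and cannot absorb correlation between people. A two-sample t-test assumes that all participants are independent.

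What is at stake is the strict 0.0083 pairwise threshold, which the plan adopts to protect two primary outcomes and three comparisons, and the 80% power claimed at that threshold. The article justifies putting the stratification factors in every model by the need for an unbiased variance. The same reasoning applies to the delivery group.

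**Working it through.** **1. The plan's own figure.** Standardised effect 0.46 (Secondary outcomes) at the secondary pairwise level 0.0167 and 80% power:

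n = 2 × (2.393 + 0.842)² / 0.46² = 98.9, so 99 per arm; 99/0.80 = 123.75, so 124; 3 × 124 = 372.

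The stated size is reproduced. Dropout is the only inflation, so no design effect is included.

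**2. Primary comparisons.** With 99 completers per arm, two-sided 0.0083 and 80% power, the non-central t gives a detectable d of 0.499. The article gives no standard deviations, so the 17.6% and 9.6% cannot be checked independently. The steps below need only d.

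**3. Group size.** 37.2/3 = 12.4 per arm per wave; two waves give 24.8. This fits the stated session range. Sessions mixing both strength arms would hold about 24.8 from one wave and 49.6 from two. At 80% retention, m = 9.9 (one wave) or 19.8 (two waves).

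**4. Formulas.** The ICC is an assumption, shown over 0.01–0.05.

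- Design effect: DE = 1 + (m − 1) × ICC. The true standard error is √DE times the unadjusted one.
- True error of the unadjusted test: 2 × [1 − Φ(2.64/√DE)].
- Power: non-central t with effect 0.499/√DE, 99 per arm, 196 df, level 0.0083.

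Both compared arms clustered:

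| m | ICC | DE | √DE | True error | Power |
|---|---|---|---|---|---|
| either | 0 | 1.00 | 1.00 | 0.0083 | 80% |
| 9.9 | 0.01 | 1.09 | 1.04 | 0.011 | 76% |
| 9.9 | 0.02 | 1.18 | 1.09 | 0.015 | 71% |
| 9.9 | 0.05 | 1.45 | 1.20 | 0.028 | 60% |
| 19.8 | 0.01 | 1.19 | 1.09 | 0.015 | 71% |
| 19.8 | 0.02 | 1.38 | 1.17 | 0.024 | 63% |
| 19.8 | 0.05 | 1.94 | 1.39 | 0.058 | 44% |

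**5. Only one compared arm clustered.** This may be the case for comparisons with control. DE is replaced by (DE + 1)/2. With m = 9.9 and ICC 0.01, 0.02 and 0.05, the true error is 0.010, 0.011 and 0.017, and power is about 78%, 76% and 70% (69.5% by the non-central t).

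**6. Cost in degrees of freedom of modelling the group.** If each arm had 10 one-wave groups, there would be 30 groups and 30 − 3 = 27 between-group df, or 27 − 9 = 18 with wave as a fixed effect. The critical t at 0.0083 rises from 2.67 (196 df) to 2.85 (27 df) or 2.96 (18 df). Power at ICC = 0 and d = 0.499 falls from 80% to about 74% or 70%. The power column in step 4 uses 196 df and does not include this loss.

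**The case against.** **No ICC is documented, and it could be near zero.** Loads are set from each person's own 1RM, most of the listed adherence techniques are individual, and the article does not say that staff differ between groups. This stands. A reader might infer that the standard errors are certainly too small; the article supports only the conditional statement.

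**The power may have slack.** The t-test ignores baseline adjustment, which the model includes. Suppose the planning standard deviation is unadjusted and the ICC is on the residual scale. The variance then shrinks by (1 − ρ²). An assumed baseline correlation of 0.4 gives 84% power at ICC 0.01 and 80% at 0.02; a correlation of 0.5 gives 89%, 86% and 76% at ICC 0.01, 0.02 and 0.05. So it is tempting, but wrong, to say that 80% power is reached only if the ICC is exactly zero. Baseline adjustment does not repair the error rate.

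**The cluster is partly inferred.** The article does not say outright that sessions are arm-specific, and sessions may merge waves. The session size is stated for strength training only. A reader might take each arm to be ten fixed groups of twelve and apply the two-arm figures to every contrast. The text supports neither step, and comparisons with control may be closer to step 5.

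**Random effects may be specified elsewhere.** The article calls the model a mixed effects model and neither lists nor excludes random effects, and the SAP is not shown. This is fair for the model. It does not cover the power calculation, whose method is stated and whose inflation is fully accounted for by retention.

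**Conclusion.** The point holds conditionally. As stated, neither the model nor the power calculation allows for correlation within a training group, although delivery is plainly by group and the figures indicate arm-specific sessions. If the ICC is positive, high versus low intensity is the comparison most clearly affected. For an assumed ICC of 0.01–0.05 in both arms, the nominal 0.0083 becomes 0.011–0.028 with about 10 completers per group, or 0.015–0.058 with about 20. Power before any baseline-adjustment gain is 76%–60% or 71%–44%. If only one compared arm is clustered, power is about 78%–70% with about 10 per group. At ICC = 0 the stated error rate and power stand.

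The range rests on the assumed ICCs, equal group sizes and 80% retention. A reader might also conclude that the trial is too small or that every model must be rewritten. With no ICC documented and a real cost to the group-level model, the article supports neither conclusion.

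**What to change.** - Record each participant's actual training group, which may combine two waves. Do not assume that wave by arm is the unit.
- Prespecify, at least as a sensitivity analysis of both primary outcomes, the stated model plus a random intercept for training group. Fit it by REML with small-sample degrees of freedom such as Kenward–Roger; the primary model as written uses maximum likelihood, so estimation changes too. Treat the control arm according to how workshops are actually grouped.
- Report the estimated ICC for each primary outcome.
- State that the 80% power assumes no within-group correlation, and give the range above, noting that it is before any gain from baseline adjustment.
- Leave enrolment unchanged.

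The data cost is small: one recorded variable and one additional model per primary outcome. The statistical cost is wider intervals and a real loss of degrees of freedom, to about 18–27 between groups with one-wave groups and fewer if waves merge. Power could be up to about 6–10 points lower even at ICC = 0. For that reason a sensitivity analysis is the minimum asked for, not a mandatory change to every primary and secondary model.

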#### High-intensity intervention (H)

The H group performs 3 sets of each exercise at 75-90% of 1RM, within the intensity range necessary to maximize muscular hypertrophy [8]. Each block has the following structure and is repeated with training loads recalibrated to each new 1RM:

Weeks 1–2. 3 sets by 8 reps. Intensity: 75% of 1RM

Weeks 3–4. 3 sets by 8 reps. Intensity: 80% of 1RM

Weeks 5–6. 3 sets by 6 reps. Intensity: 85% of 1RM

Weeks 7–8. 3 sets by 4 reps. Intensity: 90% of 1RM

Week 9. Taper. Alternate exercises and 1RM testing

Most participants have no difficulty progressing at 2-wk intervals, but variation is inevitable. Participants will rate perceived exertion (RPE) at completion of each workout. On a 10-point Borg category ratio-RPE scale, the H group should be working between 5 (hard)-8 (very hard), and the L group between 2 (easy)-4 (somewhat hard) [45]. At the end of each block, we add taper periods—2 days (Monday, Friday) of alternate exercises using Thera-Bands, separated by a 1RM testing day (Wednesday)—because the use of Thera-Bands has been shown to increase performance in older women [46].

#### Low-intensity intervention (L)

The L group performs 3 sets of 15 repetitions at 30-40% of 1RM using the exercises described above. Each 8-week block has the following structure:

Weeks 1–2. 3 sets by 15 reps. Intensity: 30% of 1RM.

Weeks 3–4. 3 sets by 15 reps. Intensity: 35% of 1RM.

Weeks 4–6. 3 sets by 15 reps. Intensity: 40% of 1RM.

Weeks 7–8. 3 sets by 15 reps. Intensity: 35% of 1RM.

Week 9. Taper week. Alternate exercises and 1RM testing

Repeat weeks 1–8 with training loads recalibrated to each new 1RM.

The workloads for the H and L groups are equated (Table 2).

**Table 2 T2:** Sample workloads and total volume for high- and low-intensity interventions, assuming 1RM = 100 lbs

**Intervention**	**Sets/Repetitions/Intensity**	**Volume**
**Low Intensity**		
Weeks 1-2	3 sets of 15 reps at 30% 1-RM	45 reps*30 lbs = 1350 lbs* 2 wks = 2700 lbs
Weeks 3-4	3 sets of 15 reps at 35% 1-RM	45 reps*35 lbs = 1575 lbs* 2 wks = 3150 lbs
Weeks 5-6	3 sets of 15 reps at 40% 1-RM	45 reps*40 lbs = 1800 lbs*2 wks = 3600 lbs
Weeks 7-8	3 sets of 15 reps at 35% 1-RM	45 reps*35 lbs = 1575 lbs* 2 wks = 3150 lbs
**Weeks 1 thru 8**		**Total volume = 12600 lbs**
**High Intensity**		
Weeks 1-2	3 sets of 8 reps at 75% 1-RM	24 reps*75 lbs = 1800 lbs*2wks = 3600 lbs
Weeks 3-4	3 sets of 8 reps at 80% 1-RM	24 reps*80 lbs = 1920 lbs*2wks = 3840 lbs
Weeks 5-6	3 sets of 6 reps at 85% 1-RM	18 reps*85 lbs = 1530 lbs*2wks = 3060 lbs
Weeks 7-8	3 sets of 4 reps at 90% 1-RM	12 reps*90 lbs = 1080 lbs*2 wks =2160 lbs
**Weeks 1 thru 8**		**Total volume = 12660 lbs**
		**Low/High Ratio = 1.0**

Total volume = total repetitions _*_ intensity _*_resistance (assume 100 lbs).

#### Healthy living education

The control group is modeled after the Arthritis Diet and Activity Promotion Trial’s (ADAPT) healthy lifestyle comparison group [47], providing attention, social interaction, and health education. Participants attend 60-min organized workshops bi-weekly for the first 6 months and monthly thereafter. This arm aims to control for attention from study staff and general levels of participant time; to encourage recruitment, adherence and benefit; and not to influence the primary outcomes directly: no evidence suggests that health education alone will affect pain or knee-joint loads during walking. The decision to use a tapered schedule is based on careful consideration of science, adherence, and expense. The control group is not matched hour-for-hour to the intervention groups but reflects the way community health-education programs are typically offered and the observation that older adults are less likely to attend more often.

Over the 18 months, interactive presentations cover such topics as hearing loss, nutrition, managing medication, and sleep practices, and experts will give wide-ranging lectures. An experiential component encourages participants to seek more information about their health and related practices. They are asked to complete homework, review topics, and engage in small group discussions to increase their involvement in this study arm. Each workshop ends with seated upper body stretching to enhance adherence and increase perceived benefit without directly affecting the knees or study outcomes. Prior studies suggest older adults are less likely to participate if they think any treatment group does not provide personal benefit.

#### Techniques to improve adherence and retention

Time-intensive behavioral studies require significant commitment [47-49]. START’s design evolved from social cognitive theory (SCT), group dynamics, and over 22 years’ experience in randomized controlled trials: our 18-month trials Fitness Arthritis and Seniors Trial (FAST), ADAPT, and Intensive Diet and Exercise for Arthritis (IDEA) had between 80%- 88% retention and 58-70% adherence. We estimate 80% retention and 65% adherence rates over the intervention; adherence is calculated by dividing the total number of sessions completed by the number scheduled.

START interventionists are trained by our health psychologist in standardized behavioral techniques developed in a SCT framework. They include frequent contact during the intervention; positive feedback; incentives to reach attendance and performance goals; establishing personal commitment to the project; and targeted mechanisms for behavioral adherence, including self-efficacy, outcome expectations, and self-regulatory skills. The importance of regular attendance is emphasized with study participants on an ongoing basis. Adherence data are reviewed regularly to identify any participants who need additional reminders and/or counseling. Our toolbox approach, guided by algorithms of common strategies and decision-making processes, tailors the intervention to each participant’s needs. For example, if a participant misses two consecutive sessions and has no contact with the interventionist, a phone session is scheduled. The interventionist assesses participant study goals and barriers to participation. Together, participant and interventionist develop a specific plan. Collectively, these strategies increase social cognitive mechanisms for regular participation and enhanced adherence in all groups.

### Trial conduct

#### Recruitment

The 30-month recruitment period is divided into 10 waves of approximately 37 participants each, entering the study at 3-month intervals. The predominant recruitment strategy is newspaper advertisements. Other recruitment efforts include mass mailings, presentations at local aging service networks, senior centers, churches, radio, and on-line advertising. Our Claude D. Pepper Older Americans Independence Center recruitment core also has access to a large database of older adults who have consented to be contacted about participation in clinical trials. Specific strategies aim to maximize the number of African Americans who qualify for, and are enrolled in, the study. At biweekly meetings, all recruitment activities and the number of participants randomized are reviewed.

### Measurements

#### Screening and follow-up visits

Those who are eligible after prescreening (PSV) sign an informed consent and attend 2 screenings (SV) and a randomization visit (RV). All 372 participants are measured at baseline, 6-, 12-, and 18-month follow-ups (FU) (Figure 2 and Table 3).

**Figure 2 F2:**
[figure not shown]
Participant eligibility and screening flow chart.

**Table 3 T3:** Data-collection visits

**Measurements**	**PSV**	**SV1**	**SV2**	**RV**	**FU6**	**FU12**	**FU18**
randomization				x			
informed consent		x					
eligibility questionnaire	x						
medical history	xc	x			x	x	x
WOMAC		x	x		x	x	x
PASE scale		x			x	x	x
MoCA		x			x	x	x
CES-D		x			x	x	x
SF-36 (general health, quality life)		x			x	x	x
Self Efficacy		x			x	x	x
6-min walk		x			x	x	x
Demographics		x					
Brief physical exam		x					
Medication Form		x			x	x	x
Knee A-P x-ray		x					x
Knee x-ray skyline view		x					
Full length lower extremity x-ray		x					
height	xc	x					
weight	xc	x			x	x	x
Waist/Hip circumference			x		x	x	x
DXA			x				x
CT scans: thigh				x			x
Biomarkers: blood				x			x
Biomarkers: urine				x	x		x
Gait Analysis			x		x		x
Muscle function tests: Power, Strength			x		x	x	x

#### Screening

The Eligibility Questionnaire addresses joint pain, physical function, activity level, co-morbid diseases, willingness to participate for 18 months, height and weight (to determine BMI), caregiver status, status of significant others, and distance of home from the center (within 50-mile radius). A study physician and a physician assistant perform routine medical exams. A score of <20 on the Montreal Cognitive Assessment (MoCA) [50,51] will justify exclusion because cognitively impaired persons may not be able to adhere to the protocol; persons scoring >17 on the Center for Epidemiologic Studies Depression scale (CES-D) [52] are evaluated by the study physician, who determines eligibility.

#### Western Ontario McMasters Universities Osteoarthritis Index (WOMAC)

Self-reported pain (primary clinical outcome) and physical function are measured using the Likert version of WOMAC [53]. The pain index assesses participants’ pain on a scale, ranging from 0 (none) to 4 (extreme). The pain subscale consists of 5 items and total scores can range from 0–20, with higher scores indicating greater pain. This instrument is recommended by the Osteoarthritis Research Society International as the health status measure of choice for older adults with knee OA. It has been validated for use in orthopaedic and pharmacologic interventions [53,54]. The pain subscale will be used only as a screening tool during SV1 (pain must be > 3). It will also be administered to the eligible participants at SV2 and each scheduled follow-up visit.

For physical function, the Likert version asks participants to indicate on the same scale from 0 (none) to 4 (extreme) the degree of difficulty experienced performing activities of daily living in the last 48 hours due to knee OA. Individual scores for the 17 items are totaled to generate a summary score that can range from 0–68, with higher scores indicating poorer function.

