Significant co-morbid disease that would threaten safety or impair ability to participate in interventions or testing, previous acute knee injury, bilateral severe tibiofemoral OA, severe patellofemoral OA (JSN = 3 using OARSI atlas), no definite medial tibiofemoral OA, severe obesity, low weight.	Symptomatic or severe coronary artery disease; severe HTN; active cancer other than skin cancer; anemia; dementia; liver disease; COPD; peripheral vascular disease; inability to walk without an assistive device; blindness; type 1 diabetes; type 2 diabetes on thiazolidinedione agents; bilateral severe medial tibiofemoral OA (KL = 4), no definite medial tibiofemoral OA (KL = 0, 1), BMI < 20 or > 45 kg^.^m^-2^	Medical history; physical exam; PA and skyline knee x-ray; height and weight.
OA disease location and alignment restrictions: predominant knee OA other than medial tibiofemoral OA; valgus, or extreme varus alignment.	Lateral tibiofemoral OA > medial tibiofemoral OA, severe patellofemoral OA; valgus knee alignment > 2°, or varus alignment > 10°	Knee PA and skyline view x-rays, lower extremity long x-ray.
Excess alcohol use	≥ 21 drinks per week	Questionnaire
Inability to finish 18-month study or unlikely to be compliant	Lives > 50 miles from site or planning to leave area ≥ 3 months during the next 18 months	Questionnaire, interview
Conditions that prohibit CT	BMI > 45 kg^.^m^-2^	height and weight
Significant cognitive impairment	diagnosis of dementia or a MoCA score <20	Medical history, MoCA
Low Pain	Pain ≤ 3 on a scale from 0-20	WOMAC

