##### Primary aim

The primary aim is the treatment effect on knee pain and maximal compressive force at 18 months. These and all other repeated measures continuous outcomes will be assessed using a mixed effects model including time (6 and 18 months), treatment group, the time × treatment interaction, and further adjusted for gender, baseline BMI, and baseline values of the outcome (i.e., baseline knee pain for knee pain model, baseline compressive force for compressive force model). The treatment effects at 18 months are tested by applying contrast statements to the mixed model, and maximum-likelihood techniques will be used to estimate parameters under the assumption of an AR(1) covariance structure. Each primary outcome will be analyzed at the Bonferroni-adjusted 0.025 level of significance, and pairwise comparisons between intervention groups at 18 months will use a 0.0083 two-sided level of significance (2 outcomes, 3 interventions) [88]. Preliminary analyses are conducted to check the shape of the distributions and variances between groups and as a function of the covariates to ensure residuals are approximately normally distributed. Regression diagnostics and residual plots help find appropriate transformations if necessary. In subsequent models, we will control for possible confounders, including PF OA severity (none to moderate) and use of medications, such as analgesics, NSAIDs, bisphosphonates, and glucosamine/chondroitin sulfate. Because we exclude subjects with severe PF OA and medication has only modest efficacy in OA, we do not expect significant confounding by these variables.

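### WOMAC pain is measured twice before randomisation, but only one reading enters the pain model; adding the SV1 score as a covariate would be a small, free gain in precision

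*Protocol article*

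**What the plan says.** Under Screening and follow-up visits, those who pass prescreening and consent "attend 2 screenings (SV) and a randomization visit (RV"). Table 3 marks WOMAC at SV1 and SV2 and places randomisation at the later visit.

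The WOMAC section limits the role of the first score: "The pain subscale will be used only as a screening tool during SV1 (pain must be > 3"). It then says of the pain subscale: "It will also be administered to the eligible participants at SV2 and each scheduled follow-up visit". Table 1 gives the matching exclusion, "Pain ≤ 3 on a scale from 0-20".

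Under Primary aim, pain is one of two primary outcomes: "The primary aim is the treatment effect on knee pain and maximal compressive force at 18 months". The mixed model adjusts each outcome for its own baseline ("baseline knee pain for knee pain model, baseline compressive force for compressive force model"). The visit that supplies baseline pain is not named, but the WOMAC section leaves only SV2. No section uses the SV1 score in an analysis.

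**The concern.** Every randomised participant should have two pre-randomisation readings of a primary outcome, because nobody can be eligible without an SV1 pain score. The model uses one of them. If each reading carries measurement error, two together predict 18-month pain better than one, and the residual variance of the pain comparison is slightly larger than the collected data allow.

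What is at stake is precision alone. The pairwise tests on pain are run at a strict level ("pairwise comparisons between intervention groups at 18 months will use a 0.0083 two-sided level of significance"), and 20% loss to follow-up is expected, so a gain that needs no new data is worth having. Neither the validity of the comparison nor the planned sample size is in question.

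**Working it through.** **Can SV1 be used without bias?** SV1 precedes randomisation, and the cut at 3 applies identically to all three arms. Given eligibility, SV1 is therefore independent of treatment assignment. Adjusting for it beside SV2 leaves the between-arm contrast unbiased. Truncation weakens its predictive value but does not remove it.

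**The plan's own figures.** Sample-size calculations gives 372 participants (124 per group), 80% retention, two-sided 0.0083, 80% power and a pain difference of 1.12 points (18%).
- Evaluable per group: 124 × 0.8 = 99.2; in total 372 × 0.8 = 297.6, about 298.
- Detectable standardised difference: (2.640 + 0.842) × √(2/99.2) = 0.494.
- Implied SD: 1.12/0.494 = 2.27. Implied mean: 1.12/0.18 = 6.2, or 1.12/0.176 = 6.4 using the 17.6% that the section also states.

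The SD is not stated, so the sample size cannot be reproduced independently. Feeding 2.27 back gives 100 per group, 125 after dropout and 375 in total, against 372, but that check is circular. The calculation is a two-sample t-test without baseline adjustment, so nothing in it depends on how SV1 is used.

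**Gain from the second reading, ignoring truncation.** Let ρ be the correlation of each reading with 18-month pain and r the correlation between SV1 and SV2. Neither is given, so both are assumptions. The residual variance factor is 1 − ρ² with one reading and 1 − 2ρ²/(1 + r) with two equally reliable readings. At ρ = 0.5 and r = 0.7:
- one reading: 1 − 0.25 = 0.750
- two readings: 1 − 0.50/1.7 = 0.706
- reduction: 1 − 0.706/0.750 = 5.9%

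**Gain with the eligibility cut.** Scores were simulated as trivariate normal, rounded and clipped to 0–20, and kept only if SV1 > 3. Residual variance of 18-month pain given SV2 alone was compared with that given SV1 and SV2. With mean 6.3 and SD 2.27, the percentage reduction is:

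| ρ | r = 0.6 | r = 0.7 | r = 0.8 | r = 0.9 |
|---|---|---|---|---|
| 0.3 | 1.9 | 1.4 | 1.0 | 0.5 |
| 0.4 | 3.7 | 2.8 | 1.9 | 1.0 |
| 0.5 | 6.6 | 4.8 | 3.3 | 1.8 |
| 0.6 | 11.1 | 8.2 | 5.5 | 3.0 |

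With mean 6 and SD 3 instead, the range is 0.5% to 10.0%, and 4.4% at ρ = 0.5, r = 0.7. The result is not sensitive to the assumed mean and SD.

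**Equivalent completers**, 298 × (1/ratio − 1), where ratio is the residual variance with both readings over that with SV2 alone:
- ρ = 0.5, r = 0.7: 298 × (1/0.952 − 1) = 15 with SD 2.27; 298 × (1/0.956 − 1) = 14 with SD 3.
- Weakest corner (ρ = 0.3, r = 0.9): 298 × (1/0.9948 − 1) = 1.6.
- Strongest corner (ρ = 0.6, r = 0.6): 298 × (1/0.8892 − 1) = 37.

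The simulation omits the BMI and gender terms and the 6-month outcome of the planned mixed model, so it gives the order of size only.

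**The case against.** The strongest reply is that nothing here is wrong. Screening on one reading and taking a fresh one as baseline is a recognised guard against regression to the mean, and the WOMAC and Primary aim sections agree with each other. In the simulations the SV1 mean exceeds the SV2 mean by about 0.1 to 0.4 points, so the guard has a purpose. All of this stands. It supports reporting SV2 as baseline; it does not argue against SV1 as a covariate.

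The practical effect is also small. If 2.27 is taken as the unadjusted SD, then at ρ = 0.5 and r = 0.7 without truncation, power for 1.12 points is already 91.6% with one baseline and becomes 93.4% with two. If the two visits are close together, r could be 0.9 and the gain 0.5% to 3%. This stands too and sets the weight of the point. A reader might infer from the 0.0083 level that the pain comparison is short of power; the document's figures do not show that.

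The same argument could be made for other prognostic measures taken at SV1. But a second reading of the outcome itself has the clearest claim, and it is the one that the text expressly sets aside. An article may leave covariate details to a fuller document, but the restriction of SV1 to screening is stated outright.

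Two further inferences are unsupported. One might point to the simulated share of randomised participants scoring 3 or less at SV2 as evidence that a single reading is noisy. That share (5–7% with SD 2.27, 9–13% with SD 3, for r of 0.6 to 0.8) only restates the assumed reliability. One might also extend the change to WOMAC function. Table 3 lists WOMAC without subscales, and the text mentions only the pain subscale at SV1, so nothing shows that function was collected then.

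**Conclusion.** The point holds as an optional improvement in efficiency. The pain model can use a second pre-randomisation reading, already collected for everyone, without biasing the arm comparison. The reduction in residual variance is about 0.5% to 11% for SV1–SV2 correlations of 0.6 to 0.9 and correlations with 18-month pain of 0.3 to 0.6. At 0.7 and 0.5 it is about 4% to 5%, or 14 to 15 completers on 298. All of these correlations are assumed.

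A reader might go further and call this an error, a contradiction or a wasted measurement. The document supports none of these: the SV1 score does its job in determining eligibility, and the single-baseline analysis is valid.

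**What to change.** In the WOMAC section, state that SV1 pain serves for screening and as an additional covariate. Under Primary aim, adjust the pain model for SV2 and SV1 pain as separate linear terms, and name SV2 as the reported baseline. This also settles which visit supplies baseline pain, which is now left to inference. Make the change before outcome data are examined by arm.

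The cost is a sentence in one section, a covariate in another and one degree of freedom. There is no new visit, no new data and no change to eligibility or sample size.
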